## Abstract

**Background:**

Vestibular rehabilitation is a safe and effective exercise-based treatment for patients with chronic vestibular symptoms. However, it is underused in general practice. Internet-based vestibular rehabilitation (Vertigo Training), which has proven to be effective as well, was developed to increase uptake. We now aim to improve the quality of care for patients with vestibular symptoms by carrying out a nationwide implementation of Vertigo Training. We will evaluate the effect of this implementation on primary care.

**Methods:**

Our implementation study consists of three successive phases:

1) We will perform a retrospective observational cohort study and a qualitative interview study to evaluate the current management of patients with vestibular symptoms in primary care, in particular anti-vertigo drug prescriptions, and identify areas for improvement. We will use the results of this phase to tailor our implementation strategy to the needs of general practitioners (GPs) and patients.

2) This phase entails the implementation of Vertigo Training using a multicomponent implementation strategy, containing: guideline adaptations; marketing strategy; pharmacotherapeutic audit and feedback meetings; education; clinical decision support; and local champions.

3) In this phase, we will evaluate the effect of the implementation in three ways.

a. Interrupted time series. We will use routine primary care data from adult patients with vestibular symptoms to compare the number of GP consultations for vestibular symptoms, referrals for vestibular rehabilitation, prescriptions for anti-vertigo drugs, and referrals to physiotherapy and secondary care before and after implementation.

b. Prospective observational cohort study. We will extract data from Vertigo Training to investigate the usage and the characteristics of participants. We will also determine whether these characteristics are associated with successful treatment.

c. Qualitative interview study. We will conduct interviews with GPs to explore their experiences with the implementation.

**Discussion:**

This is one of the first studies to evaluate the effect of a nationwide implementation of an innovative treatment on Dutch primary care. Implementation strategies have been researched before, but it remains unclear which ones are the most effective and under what conditions. We therefore expect to gain relevant insights for future projects that aim to implement innovations in primary care.

**Supplementary Information:**

The online version contains supplementary material available at 10.1186/s43058-023-00524-1.

Contributions to the literature
There is substantial literature on implementation strategies in primary care. However, it remains unclear which ones are the most effective.As one of the first studies to evaluate a nationwide implementation of an innovative treatment in Dutch primary care, we expect to provide relevant insights for future implementation projects.We will employ several research methods, including an interrupted time series, to evaluate the implementation. An interrupted time series is considered the strongest design when a randomised controlled trial is not feasible.By evaluating the effectiveness of the individual components of our implementation strategy, we can provide guidance to others in the development of strategies.

## Background

Vestibular symptoms, such as dizziness and vertigo, affect approximately 25% of the general population at some point in their lives [1]. These complaints are therefore frequently seen in general practice. In a significant number of patients with vestibular hypofunction, vestibular symptoms become persistent and they develop a chronic vestibular syndrome [2]. For instance, 30–40% of patients with vestibular neuritis still experience dizziness after 6 months [3]. One of the reasons includes failure of the vestibular compensation process, which involves adaptation of the nervous system to vestibular damage [4]. According to the International Classification of Vestibular Disorders, a chronic vestibular syndrome comprises chronic vestibular symptoms lasting months to years and includes features suggestive of persistent vestibular system dysfunction [5, 6]. The prevalence of chronic vestibular symptoms in the adult population ranges between 1.4 and 4.8% [7, 8].

Adequate treatment of patients with vestibular symptoms, and especially chronic vestibular symptoms, is of utmost importance because the consequences are far-reaching. Many patients experience a reduced quality of life. Older patients, for instance, may experience loneliness, isolation, and decreased self-esteem [3, 9]. Furthermore, vestibular symptoms are associated with a high financial burden as a result of increased healthcare utilisation, increased frequency of falls, and sick leave [8, 10].

Vestibular rehabilitation (VR) is an exercise-based treatment that stimulates vestibular compensation. It is proven to be a safe and effective treatment for both patients with unilateral vestibular hypofunction (e.g. vestibular neuritis), and bilateral vestibular hypofunction (e.g. vestibulopathy due to aminoglycoside ototoxicity) [11, 12]. In addition, a systematic review in 2018 showed that VR is effective in reducing symptoms in patients with chronic vestibular symptoms, regardless of the original cause [13]. Despite strong scientific evidence, VR is underused in general practice, mostly due to a lack of knowledge [14, 15]. In contrast, off-label anti-vertigo drugs are prescribed regularly, despite low quality of evidence [16–18].

Safe and effective self-help applications for VR have been developed to increase uptake in the United Kingdom and the Netherlands [19, 20]. In 2017 we developed Vertigo Training, a Dutch version of internet-based VR, and performed a large randomised controlled trial (RCT) [20]. Adults aged 50 years and older with chronic vestibular symptoms were randomised to stand-alone VR, blended VR (with physiotherapy support), and usual care. Patients in both the stand-alone group and blended VR group experienced a clinically relevant decrease in vestibular symptoms, dizziness-related impairment, anxiety, and depressive symptoms up to 36 months follow-up [21].

### Study aims and hypotheses

With this study, we aim to improve the quality of care for patients with chronic vestibular symptoms by carrying out a nationwide implementation of Vertigo Training, using a multicomponent implementation strategy. We hypothesise that the implementation will enhance knowledge on (the management of) chronic vestibular symptoms, in both healthcare providers and patients. As a result of this, VR referrals will increase and anti-vertigo drug prescriptions will decrease. Therefore, the first aim of this study is to determine the effect of the implementation on primary care for patients with vestibular symptoms. Our second aim is to gain more insight into the effectiveness of the individual components of our implementation strategy, as this might inform future implementation projects. After all, a systematic review in 2015 showed that it is still unclear which implementation strategies are most effective in primary care and under what conditions [22]. This protocol describes our implementation study in which we employ both quantitative and qualitative research methods.

## Methods

This implementation study consists of three successive phases with different research methods. Phase 1 is a pre-implementation phase, phase 2 includes the implementation, and phase 3 entails the evaluation of the implementation. An overview of the phases including employed research methods and measured outcomes is shown in Fig. 1.

**Fig. 1 Fig1:**
[figure not shown]
Overview of the implementation study including employed research methods and measured outcomes. *R* = Reach,* E* = Effectiveness,* A* = Adoption,* I* = Implementation,* M* = Maintenance,* GP* = general practitioner,* PT* = physiotherapist*, VR* = vestibular rehabilitation

We used the RE-AIM (Reach, Effectiveness, Adoption, Implementation, Maintenance) framework, a frequently used framework for planning and evaluating implementation [23], to develop the multicomponent implementation strategy. Furthermore, we will apply this framework to evaluate the implementation both during the implementation period, in order to adapt the strategy accordingly, as well as after this period. The RE-AIM framework has been applied in over 450 publications, covering many different populations, settings, and health conditions [24].

## Phase 1: evaluation of anti-vertigo drugs in primary care

In this phase, we will evaluate the current management of patients with vestibular symptoms in primary care, in particular anti-vertigo drug prescriptions, and identify areas for improvement. We will use the results of this phase to tailor our implementation strategy to the needs of general practitioners (GPs) and patients.

### Retrospective observational cohort study

#### Study design and data collection

We reported this retrospective observational cohort study in line with the Strengthening the Reporting of Observational Studies in Epidemiology (STROBE) Statement (Additional file 1) [25]. We will evaluate prescribing practices for anti-vertigo drugs by investigating both the prevalence and incidence of (long-term) prescriptions and characteristics associated with long-term prescriptions.

We will use anonymised routine primary care data from more than 1.2 million patients registered at 269 general practices. In the Netherlands, almost all noninstitutionalised citizens are registered with one particular GP. The included general practices participate in the Intercity Collaboration [26], which comprises academic networks of general practice at the university medical centres of Amsterdam (Academic Network of General Practice Amsterdam UMC (ANHA)), Utrecht (Julius General Practitioners’ Network (JGPN)), Groningen (Academic General Practitioner Network Northern Netherlands (AHON)), and Maastricht (Research Network Family Medicine (RFNM)). These networks run ongoing longitudinal databases containing pseudonymised data extracted from electronic patient records of the participating general practices. The databases can conditionally be used for scientific research that is relevant for (primary) care. Patients are informed about this by their GP. The databases contain data of all registered patients, except for those who objected to this (opt-out).

For this study, data will be selected from patients, aged 18 years and older, with vestibular symptoms and/or prescriptions for anti-vertigo drugs from the period March 2018 to March 2021. Patients with vestibular symptoms will be identified with International Classification of Primary Care (ICPC) codes and patients with prescriptions for anti-vertigo drugs will be identified with Anatomical Therapeutic Chemical (ATC) codes. The list of used ICPC and ATC codes is detailed in Table 1.

**Table 1 Tab1:** ICPC codes^a^ and ATC codes^b^ used for identification of patients and prescriptions

ICPC codes	ATC codes
N17 (Vertigo/dizziness)	N07CA01 (Betahistine)
N17.01 (Spinning dizziness)	N07CA02 (Cinnarizine)
N17.02 (Lightheadedness)	N07CA03 (Flunarizine)
H82 (Vertiginous syndrome)	N07CA52 (Cinnarizine, combinations)
H82.01 (Ménière’s disease)	
H82.02 (Vestibular neuritis)	
H82.03 (Benign paroxysmal positional vertigo)	

^a^International Classification of Primary Care codes

^b^Anatomical Therapeutic Chemical codes

We will collect data on demographic characteristics, registered ICPC codes for vestibular symptoms and comorbidity, prescriptions for anti-vertigo drugs, GP consultations for vestibular symptoms, and characteristics of the general practices (e.g. degree of urbanisation). Table 2 shows an overview of the variables, including those that are used for the interrupted time series (phase 3.1).

**Table 2 Tab2:** Overview of variables for retrospective observational cohort study (phase 1) and interrupted time series (phase 3)

	**Variable**	**Definition**
**Patient characteristics**	Age	In years at time of registration ICPC code for vestibular symptoms
	Sex	Male or female
	Diagnosed vestibular disorder	According to ICPC code (see Table 1)
	Comorbidity	According to the following ICPC codes: K86 (Hypertension uncomplicated), K87 (Hypertension complicated), K83 (Heart valve disease), K84 (Heart disease other), K75 (Acute myocardial infarction), K76 (Ischaemic heart disease without angina), T90 (Diabetes), K89 (Transient cerebral ischaemia), K90 (Stroke/cerebrovascular accident), P74 (Anxiety disorder/anxiety state), P76 (Depressive disorder), A49.02 (Polypharmacy)
**General practice characteristics**	Registered patients	Total number of patients registered at practice per year and total number of adult patients (aged 18 years and over) registered at practice per year
	Employed general practitioners	Total number of general practitioners per year with patients registered to their name
	Degree of urbanisation	Based on 4-digit postal code: not/hardly urbanised (< 1.000 surrounding addresses), moderately urbanised (1.000–1.500 surrounding addresses), strongly urbanised (1.500–2.500 surrounding addresses), and extremely urbanised (> 2.500 surrounding addresses)
**Other**	Date of registration ICPC code for vestibular symptoms	-
	Date of registration and deregistration at general practice	-
	Referral for vestibular rehabilitation^a^	As described in electronic patient record
	Prescription for anti-vertigo drug	According to the ATC code (see Table 1)
	Date of prescription	-
	Referrals to physiotherapist, ENT specialist, neurologist, and/or geriatrician^a^	As described in electronic patient record
	GP consultations	Total number of GP consultations (all types of consultations, including telephone consultations and home visits) per patient per year for vestibular symptoms

^a^Only applicable to interrupted time series

*ATC code* Anatomical Therapeutic Chemical code,* GP* general practitioner, *ICPC code* International Classification of Primary Care code

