#### Outcome measures

The main outcome is the prevalence of prescriptions for anti-vertigo drugs. Other outcomes are the incidence of prescriptions, prevalence of long-term prescriptions, and patient and/or general practice characteristics that are associated with long-term prescriptions.

The prevalence will be calculated as the total number of patients who received at least one (long-term) prescription divided by the average number of patients between March 2018 and March 2021. The incidence will be calculated as the total number of patients with new prescriptions divided by the total number of person years in the cohort per year. A prescription will be considered ‘new’ when a period of at least 6 months has passed between the last date of the prior prescription and the first date of the new prescription. Long-term prescriptions will be defined as prescriptions for 90 days or more in 12 months’ time.

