#### Analysis

We will perform descriptive statistics to determine the characteristics of patients and general practices and to calculate the prevalence and incidence of (long-term) prescriptions. A multivariable logistic regression analysis will be carried out to identify characteristics associated with a long-term prescription. We will use IBM SPSS Statistics (version 28.0) for the analyses.

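### Table 2's comorbidity list has no code for ischaemic heart disease with angina and ties comorbidity to no date, so the regression on long-term prescribing can misclassify patients

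*Protocol article*

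**What the plan says.** The Phase 1 retrospective cohort study selects adults "with vestibular symptoms and/or prescriptions for anti-vertigo drugs from the period March 2018 to March 2021". Its source is described thus: "These networks run ongoing longitudinal databases containing pseudonymised data extracted from electronic patient records of the participating general practices". Among the data to be collected are "registered ICPC codes for vestibular symptoms and comorbidity".

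Table 2 defines comorbidity by enumeration. The cardiac entries besides hypertension are "K83 (Heart valve disease), K84 (Heart disease other") and "K75 (Acute myocardial infarction), K76 (Ischaemic heart disease without angina), T90 (Diabetes"). No entry names ischaemic heart disease with angina.

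Table 2 fixes age at the time the vestibular code was registered. It lists dates for the vestibular code, the prescription, and registration and deregistration at the practice. It lists no date for comorbidity codes and no period over which they count.

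The Phase 1 Analysis section then states: "A multivariable logistic regression analysis will be carried out to identify characteristics associated with a long-term prescription". The outcome is defined as follows: "Long-term prescriptions will be defined as prescriptions for 90 days or more in 12 months’ time".

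**The concern.** A closed list decides who is exposed and who is in the reference group. With only the infarction code and the without-angina code, a patient whose ischaemic disease is recorded solely under an angina code joins the patients who do not have the disease.

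The missing date raises a second problem. A characteristic associated with long-term prescribing is most useful if it was present before the prescribing started. Table 2 gives no means of checking that for comorbidity, although it does supply dates for the neighbouring variables.

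At stake is one of the four outcomes of the Phase 1 cohort study: the patient and practice characteristics that go with long-term prescriptions. The article says Phase 1 results will be used to tailor the implementation strategy. The main outcome does not use comorbidity.

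**Working it through.** The plan gives no figure on this point to reproduce. The check is a reading of the definitions, followed by an illustration on assumed inputs.

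**Step 1: the code list.** The label of K76 excludes angina, and K75 is acute infarction. A patient coded only as having ischaemic heart disease with angina has neither. K84 is a residual heart-disease code, and nothing in the article says it covers angina. This step needs no assumption about dates, only that angina-coded ischaemic disease has its own ICPC code. The label of K76 implies that, but the article does not show it.

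**Step 2: the dates.** Two readings fit the text.

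| Reading | What follows |
|---|---|
| The period March 2018 to March 2021 also limits comorbidity codes | An infarction, TIA, stroke or depression coded only before March 2018 counts as absent unless registered again |
| The period limits only the vestibular codes and prescriptions | A comorbidity code entered after long-term prescribing began counts as a characteristic of the patient |

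The dates that Table 2 lists cannot rule out the second problem, because comorbidity codes have none.

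**Step 3: possible size of under-recording.** Let p0 be the true comorbidity prevalence without a long-term prescription and OR the true odds ratio. Let s1 and s0 be the shares of true cases that the definition captures in long-term users and in others, with no false positives. Then:

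- o = OR × p0/(1 − p0), and p1 = o/(1 + o)
- q1 = p1 × s1, and q0 = p0 × s0
- observed OR = [q1/(1 − q1)] / [q0/(1 − q0)]

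For the angina omission, s is the share of patients with ischaemic heart disease who carry K75 or K76. All inputs are assumptions. With p0 of 5%, 15% and 40%:

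| s1 / s0 | True OR | Observed OR (range over p0) |
|---|---|---|
| 0.9 / 0.9 | 1.5 | 1.45 to 1.50 |
| 0.6 / 0.6 | 1.5 | 1.36 to 1.48 |
| 0.6 / 0.6 | 1.0 | 1.0 |
| 0.9 / 0.8 | 1.0 | 1.13 to 1.20 |
| 0.8 / 0.6 | 1.0 | 1.35 to 1.49 |
| 0.6 / 0.8 | 1.0 | 0.67 to 0.74 |

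Worked example for equal capture: p0 = 0.40 and OR = 1.5 give o = 1.0 and p1 = 0.50. With s = 0.6, q1 = 0.30 and q0 = 0.24, so the observed OR is (0.30/0.70)/(0.24/0.76) = 1.36.

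Worked example for unequal capture at 20% prevalence and no true association: 0.95 against 0.85 gives q1 = 0.19 and q0 = 0.17, so the observed OR is (0.19/0.81)/(0.17/0.83) = 1.15.

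Equal under-recording therefore attenuates mildly and creates no false association. Unequal recording can create one, in either direction.

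**Step 4: what this does not cover.** The formula assumes no false positives. It does not describe the second reading, where codes entered too late count as present. The documents give nothing from which to size that.

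**The case against.** A reader might infer that comorbidity is restricted to the three-year window, that patients with fewer contacts are under-recorded, and that odds ratios for long-term prescribing are therefore inflated. The article does not support this chain. The period is attached to selecting patients by vestibular symptoms or prescriptions, comorbidity codes carry no date limit, and the source databases are longitudinal. No passage links contact frequency to recording. Differential capture can be argued from varying registration time and the 90-day threshold, but that is inference, and Step 3 shows the direction could reverse.

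It can also be said that a look-back rule is a detail an article commonly leaves to the full protocol or analysis plan. Taken alone, that is right. Here, though, Table 2 sets out which dates are listed and leaves comorbidity out, so the point concerns what the table fixes.

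On the code list, the choice of comorbidities is a judgement about covariates. The article defines no composite ischaemic variable, and K76 entered by itself measures what its label says. That stands as an argument against insisting on pooling. It does not explain why angina-coded disease belongs in the reference group.

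Finally, the regression is secondary and exploratory, Phase 2 already describes a final strategy, and no listed component is directed by comorbidity. This limits the consequence. Comorbidity nevertheless belongs to a named outcome of the cohort study.

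**Conclusion.** The point holds in limited form. The omission of ischaemic heart disease with angina is a feature of the stated list and depends on no reading of the dates. The absence of an index date and of comorbidity dates leaves the variable open to missed earlier disease on one reading and to codes entered too late on the other.

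Either can attenuate or distort the associations with long-term prescribing. Size and direction are unknown, because the article gives no prevalences or capture rates. On the assumed inputs, equal under-recording is a mild problem, and material bias would require unequal capture. It would go beyond the text to say that the associations are biased, or biased upward.

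The effect is confined to the secondary regression. The prevalence of prescriptions, the main outcome, does not use comorbidity.

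**What to change.** In Table 2:

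1. Add the ICPC code for ischaemic heart disease with angina. Pooling it with K75 and K76 into one variable is optional.
2. Extract the dates of the comorbidity codes.
3. Define comorbidity as any listed code in the available record up to cohort entry, with entry being the first vestibular code or first anti-vertigo prescription in the study period, since patients can qualify by either.

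The cost is one extra code, a date field and, where needed, a wider date range for these codes in the same extraction. The downside is that recently registered patients may have a shorter recorded history. A sensitivity analysis, for example restricted to patients with a minimum registration time before entry, can show how much this matters. The change does not make recording equal across patients, because longer registration still gives more time for codes to accumulate. It does fix which disease counts and when.
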